## Methodology

### Study design

This is a randomized, double-blinded, placebo-controlled trial via telemedicine. Eligible subjects will receive a maximum of 14 days’ treatment with Yinqiao Powder-Maxing Ganshi Decoction (with or without specified additions) or placebo, and will be followed up on days 7, 14 and 35 after receiving medication (day 0).

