### Inclusion criteria

1. Age from 18 to 65 years;2. Tested positive for COVID-19 by RATs, Deep Throat Saliva (DTS) or Throat/Nasal swab RT-PCR tests;3. Patient diagnosed with mild to moderate COVID-19 based on the “Coronavirus disease 2019 (COVID-19) Treatment Guidelines” published by National Institutes of Health, United States;4. Duration of symptoms ≤72 h (Start from the presence of the major symptoms of COVID-19: Fever: oral temperature >37.2°C, or cough score ≥2, or fatigue score ≥2);5. At the moment of screening (or within 2 h before screening), body temperature: >37.2°C6. Diagnosed with pattern of wind and heat invading the exterior (風熱犯表證) and/or pattern of intense exuberance of lung heat (肺熱熾盛證) by a registered Chinese medicine practitioner (CMP) (Diagnostic criteria are the corresponding criteria in the “Diagnosis standards for common syndromes in traditional Chinese medicine (《中醫常見證診斷標準》)” published by “Diagnostic Subcommittee of China Association of Traditional Chinese Medicine (中華中醫藥學會中醫診斷學分會)” in 2008, with ≥20 as the threshold for determination);7. Explicit declaration of willingness to participate in the study at the time of video-conference screening after reading the electronic informed consent form (written consent form will have to be signed after inclusion).

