### Study visits

#### Screening

Subjects who express interest in our study will be invited to do the screening by video-conference. The electronic informed consent form will be sent to them before the screening. The information about the study will be explained to the participants by our research staff. The eligibility assessment will only be conducted when subjects explicitly indicate that they have read the electronic informed consent form and volunteered to participate in the study at video screening. The written consent form has to be signed after inclusion at the appropriate time. To address exclusion criterion 7 on chronic liver and kidney disease, participants will be screened for chronic liver or kidney disease by asking about their past medical history. If patients’ answer is “Yes”, they will be excluded immediately; if “No”, then we will ask if any blood tests have been done in the past 6 months. If they answer “No”, the participants will be assumed to have no known liver or renal impairment and screening can continue. However, if the answer is “Yes”, then the participants who have blood test reports will be determined based on the results; For those without reports, they will be asked if any medical professional has indicated any abnormalities in liver or kidney function, and those with “Yes” will be excluded, while those with “No” will be screened on the assumption that there is no known liver or kidney impairment. In addition, if patients with symptoms such as jaundice, dark urine and oliguria, which are highly suspicious of liver and kidney impairment, will be excluded and advised to seek medical advice.

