#### Baseline randomization (day −1 or 0)

Eligible subjects will be assessed by our registered CMPs via telemedicine in this trial, during which medical history and concomitant medication will be recorded. After stratification, subjects will be randomly assigned in a 1:1 ratio to receive up to 14 days of either modified Yinqiao Powder-Maxing Ganshi Decoction (about 33.4–59.7 g each day) or placebo granules (about 33.4–59.7 g each day). Specifically, the stratified randomisation is based on age (A: “18–49 years old” and B: “50–65 years old”) and the number of vaccination (a: “received 3 or more doses - fulfilling government vaccination requirement” and b: “received 2 doses or less of vaccine - yet to be fully vaccinated”). Subjects will be divided into two groups by age: one group is “18–49 years old” and the other one is “50–65 years old”; then they will be further divided into two groups within the different age group by the numbers of vaccination: one group is “received 3 or more doses of vaccine, and the another is “received 2 doses or less of vaccine”. Four subgroups will be created after stratification and subjects in each subgroup will be randomly assigned to either the treatment or placebo group. The distribution of age and number of vaccinations between the two groups will be roughly comparable after stratified randomisation. The IMP will be prescribed by Registered CMPs and will be sent to patients by delivery service. The current Western medicine treatment can continue during the study period.

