### Study outcomes

#### Assessment

1. The time between starting medication and body temperature returning to normal and the recurrence rate of fever after momentary recovery. Each subject will be issued with the same type of oral thermometer for measurement at 9 a.m. (±2 h) and 9 p.m. (±2 h) daily, with at least 12 h between each measurement. Normal oral temperature is defined as equal to or below 37.2°C. Temperature recovery time is defined as the total number of days between medication starting date and the date of “normal oral temperature for 24 h without antipyretic” (both days inclusive). Subjects are required to measure the temperature until day 14 or on the day when the temperature has remained normal for 24 h, whichever is later.2. The negative rate of RATs at day 14 and negative conversion time. Each subject will be issued with the same type of RAT kits which can be used for at least 14 days for testing at 9 a.m. (±2 h) each day, with at least 24 h between each test. Negative conversion time is defined as the total number of days between the medication starting date and the date of securing two successive negative RAT results (both days inclusive). Subjects were required to undergo testing until day 14 or the day when two successive negative RAT results at least 24 h apart are obtained, whichever is later.3. The remission rate at day 14 and remission time of major symptoms.4. The disappearance rates at day 14 and disappearance time of symptoms. Subjects are required to record the status of their symptoms including major clinical symptoms daily at 9 p.m. (±2 h). Except for fever which is marked as ‘No’ or ‘Yes’ according to whether the oral temperature exceeds 37.2°C, other symptoms will be graded on a scale of 0–4 from “None”, “Mild”, “Moderate”, “Severe” and “Very Severe” depending on the actual feelings of the subject (“None” means the symptom is not present, “Mild” means the symptom is present but does not interfere with daily activities; “Moderate” means the symptom is present and slightly interferes with daily activities; “Severe” means the symptom is present and most daily activities cannot be done; “Very Severe” means the symptom is present and interferes with all daily activities). Major clinical symptoms include fever, cough and fatigue. Remission is defined as oral temperature ≤37.2°C, cough and fatigue score ≤1; disappearance is defined as the symptom being present at day 0 (score >0) but the symptom score is 0 at the date of recording.5. All-cause mortality at the 21st day after stopping the medication.6. Incidence of the progression to severe or critical illness during the trial. The all-cause mortality at the 21st day after stopping the medication and the incidence of the progression to severe or critical illness during the trial will be confirmed by communication with the subjects and/or other related person(s) or checking their medical record in the Hospital Authority. The definitions of severe and critical illness are based on the related definitions of “Coronavirus disease 2019 (COVID-19) Treatment Guidelines” published by National Institutes of Health (severe illness: oxygen saturation in the indoor environment of sea level <94%, oxygenation index [PaO2/FiO2] < 300 mmHg, respiratory frequency >30 breaths/min, lung infiltrates >50%; critical illness: respiratory failure, septic shock, and/or multiorgan dysfunction or failure).7. Utilization rates of antipyretic, Paxlovid and molnupiravir within 14 days and the total dosage(s) of the drug(s) used. In this study, subjects are allowed to take western medicines prescribed for the treatment of COVID-19 under the current guidelines of the Hong Kong Hospital Authority with at least 2 h’ gap between Chinese and western medicines. If oral temperature >39.0°C and continues over 4 h; or the oral temperature >39.5°C, the patient is advised to take antipyretic (paracetamol is recommended as a priority) for acute treatment. Patients need to record the amount and time of the drug(s) used.8. Oxygen saturation. For safety reasons, each subject will be issued with the same type of pulse oximeter for measurement at 9 a.m. (±2 h) and 9 p.m. (±2 h) daily, or whenever the subject decides it is necessary. If the reading is less than 94%, the patient is considered to have severe illness and has reached the end point of the study and is recommended to seek medical attention immediately. Subjects are required to measure their oxygen saturation at rest until day 14 or the time of body temperature returning to normal (continuing for 24 h) or the negative conversion time (2 successive negative RAT results), whichever is later.

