### Secondary outcomes

1. The recurrence rate of fever after momentary recovery: the incidence of fever recurrence (oral temperature > 37.2°C) within 24 hours after the patient’s temperature has normalized after treatment;2. The negative rate of RATs at day 14 and the negative conversion time (two successive negative RATs result with at least 24 hours interval);3. The remission rate of major symptoms at day 14 (oral temperature ≤ 37.2°C, score of cough and fatigue ≤ 1 (“None”, “Mild”, “Moderate”, “Severe” and “Very severe” were marked as 0 to 4 450 respectively), and continues 24 hours);4. Time of major symptoms remission: time from the start of treatment to symptoms remission (definition of symptoms remission: oral temperature ≤ 37.2°C, cough and fatigue score ≤ 1 and lasting at least 24 hours);5. The disappearance rates at day 14 and disappearance time of symptoms: the disappearance rates and time of individual symptoms of mild and moderate COVID-19 within 14 days (time defined as the period between starting medication and symptom disappearance); 6. The rate of patients whose oxygen saturation had gone below< 94% after intake of drugIMP, measured at day 14;7. Incidence of the progression to severe or critical illness during the trial;8. All-cause mortality at the 21st day after stopping the medication;9. Utilization rates of antipyretic, Paxlovid and molnupiravir within 14 days and the total dosage(s) of the drug(s) used.

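### Fever recovery and RAT conversion are timed from the first dose without requiring fever or a positive RAT at that point, which dilutes the comparison

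*Protocol article*

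**What the plan says.** **Entry.** Inclusion criterion 5 asks for fever thus: "At the moment of screening (or within 2 h before screening), body temperature: >37.2°C". It names no study device. Criterion 2 reads "Tested positive for COVID-19 by RATs, Deep Throat Saliva (DTS) or Throat/Nasal swab RT-PCR tests", so a positive RAT is not needed. Under Screening, "Subjects who express interest in our study will be invited to do the screening by video-conference".

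**Between entry and first dose.** Baseline randomization falls on day −1 or 0, and then "The IMP will be prescribed by Registered CMPs and will be sent to patients by delivery service". Study design defines day 0 as receipt of medication.

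**Readings.** Under Assessment, item 1, "Each subject will be issued with the same type of oral thermometer for measurement"; item 2 says the same of RAT kits, and item 8 says "each subject will be issued with the same type of pulse oximeter for measurement". Table 1 has no temperature, SpO2 or RAT entry in the Screening column. These readings begin on day 0, and their order relative to the first dose is not fixed.

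**Outcomes.** Assessment item 1 counts recovery time in days from the medication start date to the date of 24 hours' normal temperature without antipyretic, both days included. Item 2 counts RAT conversion from the same start date to two successive negatives. Neither requires fever or a positive RAT at the start. The definition of symptom disappearance in the same section does require the symptom to be present at day 0. Secondary outcome 6 is "The rate of patients whose oxygen saturation had gone below< 94% after intake of drugIMP, measured at day 14".

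**The concern.** A time-to-recovery outcome describes the treatment only in subjects who still have the condition when treatment starts. Here the qualifying fever is seen at a video call, the medication then travels to the patient, and the clock starts at the first dose. A fever that settles in between gives one of the shortest recovery times the definition allows, whatever was in the sachet. In the same way, a subject who entered on PCR and is RAT-negative from day 0 scores as a conversion.

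Three things are at stake: power for the primary comparison, the meaning of recovery times and RAT rates reported for each arm, and the ability to tell an SpO2 value already below 94% from a fall after intake. None can be repaired at analysis if no pre-dose reading exists.

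**Working it through.** **1. The plan's own figure.** Sample size estimation gives a difference of 0.5 days, SD 0.7, two-sided 5%, 80% power and 38 per group. The normal formula gives n = 2 × (1.96 + 0.8416)² × (0.7/0.5)² = 30.8, so 31 per group; the t-test version gives 31.8, so 32. The stated 38 is larger than its inputs require and gives 87% power by t-test (87.6% by normal approximation). The dropout step reproduces: 38/0.8 = 47.5, so 48 per group and 96 in total. The mismatch of 38 against 31 or 32 is a separate, conservative point, but it provides some reserve.

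**2. Dilution alone.** Let p be the share already afebrile at first dose, equal in both arms and with no treatment effect. The documents do not give p; 10%, 20% and 30% are assumptions. The expected difference becomes 0.5 × (1 − p). With SD held at 0.7, the standard error is 0.7 × √(2/38) = 0.1606.

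| p | Difference (days) | Difference / SE | Power, normal | Power, t-test |
|---|---|---|---|---|
| 0 | 0.50 | 3.11 | 87.6% | 87% |
| 10% | 0.45 | 2.80 | 80.0% | 79% |
| 20% | 0.40 | 2.49 | 70.2% | 69% |
| 30% | 0.35 | 2.18 | 58.7% | 58% |

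**3. Where the early recoveries sit.** These subjects also change the spread, by an amount that depends on the shortest possible recovery time, s. Because both days are counted, s cannot be 0. It is 1 if the date counted can be the start date itself, and 2 if a subject normal from day 0 completes the 24 hours on day 1. To show the effect, assume that the other subjects have means of 2.5 and 2.0 days (these means are not in the documents) and SD 0.7. The variance in an arm with mean m is then (1 − p) × 0.49 + p(1 − p)(m − s)².

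For p = 20%:
- s = 1: variances 0.752 and 0.552, pooled SD 0.81, power 57%.
- s = 2: variances 0.432 and 0.392, pooled SD 0.64, power 77%.

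| p | s = 1 | s = 2 | Febrile subjects only |
|---|---|---|---|
| 10% | 71% | 82% | 83% |
| 20% | 57% | 77% | 78% |
| 30% | 45% | 70% | 72% |

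The last column uses a difference of 0.5, SD 0.7 and 38 × (1 − p) per group, about 34, 30 and 27. With s = 2, restricting to febrile subjects gains only 1 to 2 points. With s = 1 it gains 12 to 27.

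**4. RAT and SpO2.** No arithmetic applies. For RAT, entry without a RAT combined with a conversion clock that has no starting condition means that two negatives from day 0 count as a conversion. For SpO2, the outcome is worded as a fall after intake, but no reading is fixed before intake against which to judge the first home value.

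**The case against.** **The loss may be small.** Screening and randomisation are on day −1 or 0 and symptoms must have lasted no more than 72 hours, so the wait is meant to be short and nothing in the documents supports 20% or 30%. At 10%, power is still about 79% because 38 exceeds what the inputs need. This stands, and it limits how serious the point is. The share remains unknown and, as planned, may not be measured.

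**A reader might infer immediate recovery at time zero.** The documents do not allow it. Days are counted inclusively, and 24 hours of normal temperature without antipyretic are required, so a briefly normal or antipyretic-masked temperature is not a recovery.

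**A reader might infer that pre-dose SpO2 values below 94% are counted as outcomes.** The wording does not say so. Severe illness is excluded at entry, and secondary outcome 6 is limited to values after intake. The gap is only that no fixed pre-dose reading lets the two be told apart.

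**A reader might infer a false benefit.** Allocation is 1:1 and double-blind, so affected subjects should fall about equally in both arms. The expected effect is dilution.

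**Readings are already scheduled on day 0, and their order may be in the full protocol.** Day-0 device readings are indeed planned, and an article may leave their order out. The outcome definitions are given here, however. They lack the starting condition that the same section applies to symptom disappearance.

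**Restricting the primary analysis to febrile subjects would remove randomised patients**, including some who are only briefly normal. This stands, and it is why the restriction is proposed only as supportive.

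**Conclusion.** The point holds for temperature recovery time and for the RAT outcomes: neither is conditioned on the subject still having what is to be resolved when the clock starts. The consequence is a diluted between-arm difference and single-arm times and rates that look better than they should.

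By dilution alone, t-test power falls from 87% to about 79%, 69% or 58% if 10%, 20% or 30% are already afebrile. This assumes no effect in those subjects, equal shares in both arms, SD 0.7 and 38 evaluable per group. The actual loss could be smaller or larger, depending on where the minimum recovery time falls under the inclusive count. For SpO2 the point is limited to a missing reference value. It does not undermine the validity of the comparison, but it is worth correcting before enrolment because the missing reading cannot be recovered later.

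**What to change.** 1. State that on day 0 the already scheduled oral temperature, SpO2 and RAT readings are taken with the issued devices before the first dose.
2. Compute the RAT negative rate and conversion time among subjects RAT-positive at that reading.
3. Use the pre-dose SpO2 in the analysis of secondary outcome 6 to separate values already below 94% from falls after intake.
4. Keep all randomised subjects as the primary analysis set, and prespecify a supportive analysis of the primary outcome in subjects whose pre-dose oral temperature is above 37.2°C. The reading precedes treatment and is taken under blinding, so the subset cannot be shaped by the drug.
5. State which date ends the inclusive day count, so that the minimum recovery time is known.

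The cost is one ordering instruction on a day when the readings are already due, some definition wording, and fewer subjects in the RAT analyses.

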### Exclusion criteria

• Diagnosed with Asymptomatic or Presymptomatic Infection, Severe Illness or Critical Illness of COVID-19 based on the “Coronavirus disease 2019 (COVID-19) Treatment Guidelines” published by National Institutes of Health, United States;• Known allergy to the Chinese medicines or other ingredients of the investigational medicinal products (IMP) used in this study;• Known pregnancy or lactation;• Known immunocompromised patient (such as malignancy, organ or bone marrow transplant, AIDS or low immune function caused by long-term use of corticosteroids or other immunosuppressants)• Known obesity (Body Mass Index [BMI] ≥30)• Heavy smoker (smoking index ≥400 [cigarettes smoked per day × years of tobacco use])• Known history of cardiovascular and cerebrovascular diseases (including hypertension), chronic lung disease (chronic obstructive pulmonary disease, moderate and severe asthma or interstitial lung disease), diabetes, chronic liver disease (ALT/AST ≥2× the upper limit of normal [ULN], Bilirubin-Total ≥1.5ULN), chronic kidney disease (Creatinine ≥1.5ULN), cancer;• Known presence or suspicion of acute liver or kidney diseases;• Known history of dysphagia or any gastrointestinal disorder that affects drug absorption (such as gastroesophageal reflux disease [GERD], chronic diarrhea, inflammatory bowel disease, intestinal tuberculosis, gastrinoma, short bowel syndrome, gastrectomy);• Suspected or known history of alcohol or substance abuse or mental illness;• Subjects having participated in other clinical studies in the past 3 months; and• Any other condition that in the opinion of the investigators could compromise the study.

## Study intervention

### Study medications

Yinqiao Powder-Maxing Ganshi Decoction is the core formula in this clinical study and consists of the following botanical and mineral drugs: Ephedra sinica Stapf/Ephedra intermedia Schrenk and C.A.Mey./Ephedra equisetina Bunge [Ephedraceae; Ephedrae Herba Praeparata cum Melle] (Mi-ma-huang 蜜麻黃) 6 g, Prunus armeniaca var. armeniaca/

Prunus sibirica L./Prunus mandshurica (Maxim.) Koehne/Prunus armeniaca L. [Rosaceae; Armeniacae Semen Amarum] (Ku-xing-ren苦杏仁) 6 g, Glycyrrhiza uralensis Fisch. ex DC./Glycyrrhiza inflata Batalin/Glycyrrhiza glabra L. [Fabaceae; Glycyrrhizae Radix et Rhizoma] (Gan-cao 甘草) 10 g, Gypsum Fibrosum (Shi-gao 石膏) 12 g, *Lonicera japonica* Thunb. [Caprifoliaceae; Lonicerae Japonicae Flos] (Jin-yin-hua 金銀花) 15 g, Forsythia suspensa (Thunb.) Vahl [Oleaceae; Forsythiae Fructus] (Lian-qiao 連翹) 15 g, Platycodon grandiflorus (Jacq.) A. DC. [Campanulaceae; Platycodonis Radix] (Jie-geng 桔梗) 10 g, Mentha canadensis L. [Lamiaceae; Menthae Haplocalycis Herba] (Bo-he 薄荷) 6 g, Lophatherum gracile Brongn. [Poaceae; Lophatheri Herba] (Dan-zhu-ye 淡竹葉) 15 g, Nepeta tenuifolia Benth. [Lamiaceae; Schizonepetae Spica] (Jing-jie-sui荊芥穗) 12g, Glycine max L.) Merr. [Fabaceae; Sojae Semen Praeparatum] (Dan-dou-chi 淡豆豉) 15 g, Arctium lappa L. [Asteraceae; Arctii Fructus] (Niu-bang-zi 牛蒡子) 15 g, Phragmites australis subsp. australis [Poaceae; Phragmitis Rhizoma] (Lu-gen蘆根) 30 g. At the same time, the following additions will be made according to the symptoms and pathogenesis of the patient at inclusion, in order to reflect the principle of pattern identification of Chinese medicine theory:i. Sore throat (heat accumulation in the lung and stomach熱蘊肺胃):• Isatis tinctoria subsp. tinctoria [Brassicaceae; Isatidis Radix] (Ban-lan-gen 板藍根) 15 g,• Ilex asprella Champ. ex Benth. [Aquifoliaceae; Ilicis Asprellae Radix] (Gang-mei-gen崗梅根) 15 g, Lasiosphaera Calvatia (Ma-bo 馬勃) 5 g;ii. Cough and asthma with yellow sputum or less sputum (phlegm and heat obstructing the lung痰熱阻肺): Fritillaria thunbergii Miq. [Liliaceae; Fritillariae Thunbergii Bulbus] (Zhe-bei-mu 浙貝母) 10 g, Trichosanthes kirilowii Maxim./Trichosanthes rosthornii Harms [Cucurbitaceae; Trichosanthis Pericarpium] (Gua-lou-pi 瓜蔞皮) 10 g;iii. Nausea and vomit, torpid intake (納呆) and sloppy stool (便溏) (dampness impacting the middle energizer濕阻中焦): Pogostemon cablin (Blanco) Benth. [Lamiaceae; Pogostemonis Herba] (Guang-huo-xiang 廣藿香) 10 g, *Poria* (Fu-ling 茯苓) 10 g, Atractylodes macrocephala Koidz. [Asteraceae; Atractylodis Macrocephalae Rhizoma] (Bai-shu白术) 10 g;iv. Insomnia (Heat harassing the heart spirit 熱擾心神): Ziziphus jujuba Mill. [Rhamnaceae; Ziziphi Spinosae Semen] (Suan-zao-ren酸棗仁) 10 g,v. Reynoutria multiflora (Thunb.) Moldenke [Polygonaceae, Polygoni Multiflori Caulis] (Shou-wu-teng首烏藤) 10 g, Margaritifera Concha (Zhen-zhu-mu 珍珠母) 20 g.

Subjects in the treatment group will receive CM granules in dosages equivalent to the decocting piece dosages shown above according to the IMP manufacturer’s illustration (estimated granule weight per dose: 33.4–59.7 g), and will be dissolved in hot water and administered while it is warm. Participants will take 1 dose a day, and the medication will be divided into two portions, with one in the morning and the other in the evening after meal. The time of treatment and medication is 14 days at maximum or until patients get negative RAT results on two successive days and the major symptoms subside (define as oral temperature ≤37.2°C, the score of cough and fatigue ≤1). The actual duration is determined by the patient according to their own condition, and they can also seek advice from the research team or registered CMPs though the direct phone line if necessary.

The CM granules are planned to be a mixture of single granules produced by PuraPharm, a commercial company in Hong Kong. Most of these granules are made from botanical drugs used in CM, with some made from fungi (*Lasiosphaera Calvatia, Poria*), animal (*Margaritifera Concha*), and mineral (*Gypsum Fibrosum*). They are turned into granules by using modern methods that mimic the old way of making CM decoction. PuraPharm is the main provider of these granules to Hong Kong’s hospitals and health institutions. The botanical, animal and mineral drugs meet the standards of Chinese Pharmacopoeia if they are included. This company follows the GMP standards of the PRC, Australia and the US for quality control and production. It also has an ISO 17025 certified laboratory to check the quality.

The placebo was made from Sorbitol, Maltodextrin, Corn Starch, Soluble Fiber, Black Bean Extract, Abelmoschus esculentus Extract, Green Tea Extract, Caramel Color Powder, Citric Acid and Ginseng Flavo, whose appearance, smell and taste was similar to the CM granules. Subjects will be instructed to take them in the same way as in the treatment group. Each study subject will be given relevant information on the use and storage of IMPs. The granules of both treatment and placebo group will be produced by a manufacturer with a GMP certificate.

According to Chinese Medicine Council of Hong Kong’s official website (Chinese Medicine Council of Hong Kong, 2023) “If the single Chinese medicine granules are only supplied to Chinese medicine practitioners to dispense a prescription, instead of dispensing the herbs, they do not fulfill the definition of pCm (*proprietary Chinese medicine*) and thus are not required to apply for pCm registration”. For this reason, the concentrated Chinese medicine granules used in this study are not pCms, and therefore no Certificate for Clinical Trial and Medicinal Test (CTC) is needed for this clinical study.

